#### Kansas City cardiomyopathy questionnaire

KCCQ is used to assess patients’ quality of life [14]. The KCCQ is self-administered, but patients can also complete the questionnaire by interview through a clinician. On average, it will take 4 to 6 min to complete the KCCQ.

#### Six-minute walk test

The 6MWT will be performed in an indoor hospital corridor at each participating site. The walking course is straight, flat, and at least 30 m in length. The starting line and every 3 m of the course are marked. Patients will be asked to walk along the corridor back and forth. Patients will be allowed to stop and rest or discontinue the test. The longest distance in 6 min will be measured to the nearest whole meter. In order to maintain consistency, all participating sites will use a standardized manual to guide operations, including standardized phrasing to give patients instructions and encouragement.

#### Transthoracic echocardiography protocol

Transthoracic echocardiography will be performed using commercially available ultrasound systems at each participating sites. In order to maintain consistency, all measurements will be performed according to the expert consensus on adult transthoracic echocardiography reporting [15].

#### Cardiovascular magnetic resonance protocol

CMR scanning will be performed using a 1.5-T scanner which is commercially available at local participating sites. An electrocardiography-triggering acquisition will be conducted for patients in supine position and breath-hold at the end of expiration. Late gadolinium enhancement CMR was also conducted by the administration of 0.2 mmol/kg of gadolinium. After scout imaging, the long axis of the LV and four-chamber cine images will be acquainted using the balanced steady-state free precession (bSSFP) sequence with a slice thickness of 8 mm and interslice gap of 2 mm. Imaging acquisition parameters are as follows: repetition time 34 ms, echo time 1.3 ms, flip angle 50°, average temporal resolution 35–45 ms, and field of view 280 × 340 mm^2^.

Images will be evaluated using the Cvi42 version 5.12 software (Circle Cardiovascular Imaging Inc.) for LV mass, volumes, and function. LV mass is calculated by multiplying the difference between total epicardial volume and total endocardial volume with the density of myocardium (1.05 g/mL). LV mass is then indexed to the surface area to achieve LV mass index [16].

#### Plans to promote participant retention and complete follow-up {18b}

All reasonable efforts (such as by email and telephone call) will be made to complete the data collection including follow-up information for endpoints (if applicable) and the reason why participants want to quit the trial.

### Data management {19}

A digital case reported form will be designed and used for data collection. All collected data will be stored and managed using a web-based data manage system. Researchers are responsible for the data collection, especially for checking that all data related to this trial are filled out in the data manage system correctly and completely. A data management plan will be created beforehand for data validation.

#### Confidentiality {27}

Personal data of the participants will be treated as confidential and stored securely during the whole course of this trial.

#### Plans for collection, laboratory evaluation, and storage of biological specimens for genetic or molecular analysis in this trial/future use {33}

Not applicable

## Statistical methods

### Statistical methods for primary and secondary outcomes {20a}

The primary and secondary endpoints will be analyzed according to the intention-to-treat principle. To compare the primary endpoint, adjusted mean difference in changes in LV mass index at 24-month follow-up visit between the two groups will be tested using linear regression with adjustment for baseline values. Time-to-event comparison (f.e., secondary endpoints including all-cause mortality and cardiac death) between the groups will be conducted using log-rank test and proportional hazards regression. A two-sided p value of 0.05 will be considered statistically significant.

### Interim analyses {21b}

Not applicable, no interim analysis will be performed.

### Methods for additional analyses (e.g., subgroup analyses) {20b}

For descriptive analyses of baseline characteristics, continuous variables will be presented as mean and standard deviation or median and interquartile range depends on the distribution. Categorical variables will be presented as frequencies and percentages. Differences between the groups will be tested using the independent t-test or Mann-Whitney U test when appropriate for continuous variables and using the chi-square test or Fisher’s exact test when appropriate for categorical variables.

### Methods in analysis to handle protocol non-adherence and any statistical methods to handle missing data {20c}

All efforts will be made to complete the follow-up and data collection and avoid missing data. Analyses will be conducted in complete cases. We will also perform sensitivity analyses by imputing the missing data to worst cases.

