#### Criteria for discontinuing or modifying allocated interventions {11b}

Participants are allowed to discontinue and end their participation in the trial at any time for any reason. Researchers can decide to withdraw a participant from the trial at any time when encountering emergency circumstances and/or for any urgent medical reasons.

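### The primary analysis keeps only complete cases despite the intention-to-treat statement, and its one named check, an undefined worst-case fill, does not suit a continuous outcome

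*Protocol article*

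**What the plan says.** Section {20a} sets the principle: "The primary and secondary endpoints will be analyzed according to the intention-to-treat principle". The difference in change in LV mass index at 24 months "will be tested using linear regression with adjustment for baseline values".

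Section {20c} sets the data to be used and names one check: "Analyses will be conducted in complete cases. We will also perform sensitivity analyses by imputing the missing data to worst cases". It does not say what the worst case is for a change in g/m², or whether both arms are filled in the same direction.

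Table 1 and section {18a} place CMR at baseline and 24 months only. Echocardiography and NT-ProBNP are collected at baseline and at all five follow-up visits.

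Section {11b}, which is headed as covering discontinuation or modification of the allocated intervention, speaks only of leaving the trial: "Participants are allowed to discontinue and end their participation in the trial at any time for any reason", and "Researchers can decide to withdraw a participant from the trial at any time when encountering emergency circumstances and/or for any urgent medical reasons". Section {18b} points the other way. All reasonable efforts "will be made to complete the data collection including follow-up information for endpoints (if applicable"), and the reasons for quitting are to be recorded.

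**The concern.** A patient needs both scans to enter the primary regression. Anyone who dies, leaves or misses a scan drops out of it, so the analysed set is not all randomised patients, even though those who remain are compared by allocated arm. Treatment is open-label and only one arm takes a titrated study drug, so loss could differ by arm and be related to outcome. The primary estimate could then favour the arm that lost more of its poorly responding patients.

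The sensitivity analysis should show whether that matters. A single extreme value placed in every gap of a continuous outcome cannot do so, because the result is driven by the number of gaps in each arm. Since the term is undefined, its meaning could also be settled after the data are seen.

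**Working it through.** **Inputs.** From section {14}: 100 per group, difference 20 g/m², SD 35 g/m², 10% dropout, alpha 0.05 (two-sided in {20a}). Assumed here: how missingness splits by arm, whether it depends on outcome, and the reading of the worst-case rule.

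**1. The plan's own figure.** With 90 completers per arm, SE = 35 × √(2/90) = 5.22, 20/5.22 = 3.83, and power = Φ(3.83 − 1.96) = 97%. The stated power of more than 90% reproduces. With 65 completers per arm, SE = 6.14 and power = Φ(3.26 − 1.96) = 90%. Power therefore holds up to about 35% missing, and the issue is bias rather than sample size.

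**2. What worst-case filling does.** Let benefit be control change minus fosinopril change, Δ the true benefit, and p_F and p_C the missing shares, missing at random within arm. The worst observed value in about 90 patients lies about 2.5 SD (87.5 g/m²) above its arm mean. In a pooled sample of about 180 with no effect, it lies about 2.7 SD (94.5 g/m²) above the mean.

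- One pooled worst value for everyone: benefit ≈ Δ(1 − p_F) − (p_F − p_C) × (distance from the control mean to the worst value).
  - Δ = 20, 10%/10%: 20 × 0.90 = 18.
  - Δ = 20, 15%/5%: 20 × 0.85 − 0.10 × 87.5 = 8.25.
  - Δ = 0, 15%/5%: −0.10 × 94.5 = −9.45.
- Each arm's own worst value: benefit ≈ Δ − (p_F − p_C) × 87.5.
  - Δ = 20: 20 at 10%/10%; 20 − 8.75 = 11.25 at 15%/5%.
  - Δ = 0, 15%/5%: −8.75.
- Worst for fosinopril, best for control, Δ = 20, 10%/10%: taking a control mean of −20 and a fosinopril mean of −40, worst ≈ −20 + 87.5 = 67.5 and best ≈ −40 − 87.5 = −127.5. Then 18 − 0.10 × 195 = −1.5.

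Simulation (4,000 runs per scenario, 100 per arm, t-test on change) agrees:

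| True effect | Missing, fosinopril/control | Complete case | Pooled worst | Own-arm worst | Worst v best |
|---|---|---|---|---|---|
| 20 | 10%/10% | 20 (power 97%) | 18 (82%) | 20 (90%) | −1.5 (2%) |
| 20 | 12%/8% | 20 (97%) | 14 (62%) | 17 (78%) | −1.5 (2%) |
| 20 | 15%/5% | 20 (97%) | 8 (25%) | 11.5 (51%) | −1.7 (1%) |
| 0 | 15%/5% | 0 | −9 (harm significant in 32%) | −8 (29%) | −19 (86%) |

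Independent runs gave 80% to 82% power for the pooled fill at 10%/10%, 33% false harm for the pooled fill at 15%/5%, and −1.7 to −1.9 for worst v best at 10%/10%.

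**3. What complete cases do to the primary.** In every row above the complete-case estimate is unbiased, because data are missing at random within arm. Bias needs outcome-dependent loss that differs by arm. Letting the chance of a missing scan roughly double per SD of worse change:

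- 10%/10%: bias about 0, type I error about 5% to 6%.
- 15%/5%: bias about 3 g/m² in favour of fosinopril, type I error about 10%.

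Simple arithmetic gives the same order. If 10% of the fosinopril arm is lost and would have done 20 g/m² worse than those who stayed, the shift is 0.10 × 20 = 2 g/m².

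**The case against.** Several points on the other side stand.

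- A reader might infer that patients who do not tolerate the drug are removed from the trial. The article does not say so. Investigator withdrawal in {11b} is discretionary and limited to emergency or urgent medical reasons, and {18b} seeks endpoint data even from those who quit. What remains is that {11b} does not separate stopping drug from leaving follow-up, and that the effort in {18b} is qualified.
- A reader might infer that the primary result is shown to be biased, or that the large distortions in the table apply to it. They apply only to the sensitivity analysis, which does not decide the trial. They also shrink with a milder split: at 12%/8% the pooled fill gives about 14, not 8.
- Intention-to-treat is often used to mean analysed as randomised, and {20c} excludes nobody for non-adherence. On that usage the two sections can coexist, but some randomised patients are still left out of the primary.
- Complete-case regression adjusted for baseline is valid if missingness depends only on arm and baseline value. The article gives no evidence against this; equally, it plans no analysis that would test it usefully.
- Section {20c} covers all endpoints, and worst-case filling is a recognised stress test for binary ones. The objection is to its use on the continuous primary.
- An unseen analysis plan may define the fill and the handling of death. The finding does not rest on their absence. It rests on the rule that the article states.

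**Conclusion.** The point holds in a limited form and should be fixed. The article pairs an intention-to-treat statement with a complete-case primary. Its only named check can return anything from near-confirmation (about 18 to 20) to loss of the whole effect (about −2) on the same 10%/10% missingness, depending on how one undefined term is read. With 15% v 5% missing it can also produce 8 to 9 g/m² of apparent harm where there is none, under either same-direction reading.

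For the primary estimate the risk is conditional: about zero with equal loss, and about 2 to 3 g/m² (10% to 15% of the 20 g/m² target) with unequal, outcome-dependent loss. These figures rest on assumed rates by arm and an assumed mechanism, since the article gives only 10% dropout. The exclusion of patients who die concerns the CMR primary; the mortality endpoints have their own time-to-event analysis. Neither the sample size nor the stated power is in question.

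**What to change.** 1. **Section {20c}, primary analysis.** Run the same baseline-adjusted regression with multiple imputation by arm for surviving patients with a missing scan. Use baseline CMR and the serial echocardiography and NT-ProBNP already scheduled. Keep complete case as a sensitivity analysis. State plainly that patients who die before 24 months have no imputed scan, and report mortality beside the result. The gain depends on how well echocardiography and NT-ProBNP predict CMR mass, which the article does not quantify.
2. **Section {20c}, sensitivity.** For the continuous primary, replace worst-case filling with a pre-specified delta-adjusted tipping-point analysis: worsen the imputed values step by step, by arm, and report the shift at which the conclusion changes. If worst-case filling is kept for binary endpoints, define it.
3. **Section {11b}.** State that stopping study drug does not end follow-up, and that the 24-month CMR is still sought unless the patient withdraws consent to data collection, in line with {18b}. This concerns data collection only; it does not touch when the drug is stopped.

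The cost is wording, some programming and continued follow-up of patients off drug; no new assessment is needed. A worst-rank analysis for death is optional, because it changes the question being asked. Item 3 is best settled before any follow-up is lost.

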### Plans to give access to the full protocol, participant level-data, and statistical code {31c}

Statistic plan and statistical code will be published together with the final reports after the whole trial is closed. There is no plan to release the participant-level dataset; however, access to the dataset will be possible upon reasonable requisition.

## Oversight and monitoring

### Composition of the coordinating center and trial steering committee {5d}

The coordinating center is the West China Hospital. The trial steering committee consists of principal investigators at each study site responsible for interventions (standard care for the control group, standard care plus fosinopril for the intervention group). Other clinicians of the local Heart Team will be responsible for follow-up, data collection, and logistic support for the trial. The endpoint adjudication committee consists of an imaging core lab and two cardiologists.

### Composition of the data monitoring committee, its role, and reporting structure {21a}

The data and safety monitoring committee (DSMC) will consist of four qualified members from the West China Hospital, including at least one statistician and cardiology expert independent from the site trial staff. The DSMC is independent from the trial researchers, blinded to the assignment, and will monitor the progress of the trial and safety issues and require data for analyses.

### Adverse event reporting and harms {22}

Adverse events reported by the participant or noticed by the clinician will be reported directly (maximum within a week) to the DSMC and recorded in the digital case reported form and data manage system.

### Frequency and plans for auditing trial conduct {23}

Audit reports will be given by the trained auditors at three different time points, namely after the first participant is enrolled, at 12 months after launching the trial, and before the trial is closed out. Eligibility of recruited participants, collection of consent, and data integrity will be checked at each study site.

### Plans for communicating important protocol amendments to relevant parties (e.g., trial participants, ethical committees) {25}

A yearly update will be given to the ethics committee if any protocol amendment is supposed to be made in line with the updates for clinical practice. Amendments will be made only after a favorable opinion is given by the ethical committees. All site trial staff will be informed correspondently.

### Dissemination plans {31a}

The trial results will be presented at international meetings and published in a peer-reviewed journal.

## Discussion

With the expanded utilization of TAVI to a younger and lower surgical risk patient with severe AS, optimal medical therapy after TAVI procedure has become the main concern. Interests have been drawn in the investigation of medications that can improve cardiac remodeling and long-term clinical outcomes. Currently, a routine strategy of medical therapy after the TAVI procedure is not recommended due to insufficient evidence supporting the benefits. Previous studies found that the use of RASi may have the potential to prevent or reverse cardiac remodeling and improve prognosis with less inconsistent results [8–10, 13]. Further evidence from randomized control trials is warranted to clarify the effect of RASi in cardiac remodeling and long-term prognosis. Regarding this concern, we designed this randomized control trial to investigate the effect of the prescription of RASi, specifically fosinopril, after TAVI on cardiac remodeling, clinical outcomes, and quality of life. We also summarized other randomized trials regarding this topic (Table 2). Similarly, another study in Europe, the RAS blockade after TAVI (RASTAVI) study (http://www.ClinicalTrials.gov NCT03201185), which was designed to address whether the prescription of ramipril in postoperative AS patients can be beneficial is still ongoing [17]. Together, these studies will provide further evidence regarding medical therapy for AS patients who underwent TAVI, and our study will specifically fill the gap in the Chinese population.

**Table 2 Tab2:** Summary of randomized trials that investigated the effect of renin-angiotensin system blockade therapy after aortic valve replacement for severe aortic stenosis patients

Author, year	Region	Study population	Study design	Registration	Sample size^a^	Interventions	Comparison	Primary outcomes	Status
Dahl et al., 2010 [8]	Denmark, single center	Post SAVR	Randomized, open-label, blinded endpoint	NCT00294775	61:64	Candesartan treatment	Conventional treatment	Change in LV mass index	Completed
Amat-Santos et al., 2018 [17]	Spain, 8 centers	Post TAVI	Randomized, open-label, blinded endpoint	NCT03201185	168:168	Ramipril plus standard care	Standard care	Cardiac death or heart failure hospitalization or stroke	Recruiting
Aboyans et al. [18]	France, multicenter	Post SAVR or TAVI	Randomized, quadruple blinded	NCT03315832	55:55	Valsartan	Placebo	Changes in LV mass index	Not yet recruiting
[name] et al.	China, 7 centers	Post TAVI	Randomized, open-label, blinded endpoint	ChiCTR2100042266	100:100	Fosinopril plus standard care	Standard care	Change in LV mass index	Active, not yet recruiting

*SAVR* surgical aortic valve replacement, *LV* left ventricle, *TAVI* transcatheter aortic valve intervention

^a^Number of patients in the intervention group versus the control group

## Trial status

The recruitment of this study will be started in September 2021, and the last participant will be included in September 2023 anticipatedly.

## Abbreviations

6MWT: Six-minute walk test
AS: Aortic stenosis
CMR: Cardiac magnetic resonance
DSMC: Data and safety monitoring committee
KCCQ: Kansas City Cardiomyopathy Questionnaire
LV: Left ventricular
LVEF: Left ventricular ejection fraction
NYHA: New York Heart Association
RASi: Renin-angiotensin system inhibitors
SAVR: Surgical aortic valve replacement
TAVI: Transcatheter aortic valve implantation
